### Overview of Testing Procedures

The study design and stepwise stages of the protocol are described in Figure 2. Before and following the 12-week intervention, participants completed 4 data collection sessions. At the first session, participants completed a cardiorespiratory fitness test of peak oxygen consumption (VO_2peak_), and body composition was measured by dual energy x-ray absorptiometry (DXA). At least 72 hours later, the participants spent a night at the laboratory where they were given a standardized evening meal at 8 PM and then required to fast overnight (10 hours). During the evening or early morning, participants were requested to provide a fecal sample. At 6 AM, the participants completed measures of resting metabolic rate (RMR) and substrate metabolism, and resting heart rate and blood pressure were measured. At 7 AM, fasting blood samples were collected and participants underwent a frequently sampled intravenous glucose tolerance test (FSIGT). During the FSIGT, the field worker administered the questionnaires, and the participants completed a 24-hour dietary recall and food frequency questionnaire with a Health Professions Council of South Africa registered dietician. The participants were then requested to complete a 3-day food diary. On a separate day, after a 10- to 12-hour overnight fast, participants completed steady-state exercise testing at 50% VO_2peak_. Thereafter, participants were provided a standardized meal and underwent a magnetic resonance imaging (MRI) scan. On the fourth day of data collection, and after 4 to 6 hours of fasting and 48 hours of rest, participants underwent skeletal muscle and abdominal and gluteal SAT biopsies. Accelerometers (ActiGraph and ActivPAL) were attached to the participants and worn for 7 days.

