#### Fasting Blood Samples and Frequently Sampled Intravenous Glucose Tolerance Test (FSIGT)

Following the RMR measures, fasting blood samples were drawn, and an FSIGT was performed. A cannula was inserted into a vein of each arm. One arm was used for intravenous glucose and insulin infusions, and the other arm was heated and used for blood sampling. Fasting blood samples were drawn for the determination of adipokines, myokines, inflammatory markers and cytokines, lipid profiles and HDL- and LDL-cholesterol subtypes and HDL functionality, and red blood cell fatty acid composition, metabolomic and lipidomic analysis.

For the FSIGT, further 2 baseline samples were collected at −5 and −1 min before a bolus of glucose (50% dextrose; 11.4 g/m^2^ body surface area) was infused intravenously over 60 seconds beginning at time 0. At 20 min, human insulin (0.02 U/kg; NovoRapid, Novo Nordisk) was infused over 5 min at a constant rate (HK400 Hawkmed Syringe Pump, Shenzhen Hawk Medical Instrument Co., Shenzhen, China). Samples for determination of plasma glucose and serum insulin and c-peptide concentrations were drawn at 2, 3, 4, 5, 6, 8, 10, 12, 14, 16, 19, 22, 23, 24, 25, 27, 30, 35, 40, 50, 60, 70, 80, 90, 100, 120, 140, 160, 180, 200, 220, and 240 min.

Fasting blood samples were collected into EDTA, lithium heparin, fluoride oxalate, and SST tubes. Samples in SST tubes clotted for 30 min at room temperature, while the remaining samples were placed on ice before centrifugation. Samples were centrifuged at 3000 rpm for 10 min at 4°C. Plasma for glucose analysis was stored at −20°C, while the remaining serum and plasma was stored at −80°C. Red blood cells collected from EDTA tubes were washed by 2 cycles of sequential centrifugation at 1000 rpm and a final cycle of centrifugation at 3000 rpm for 10 min. Between cycles, saline (0.9% NaCl in distilled water) was used for resuspension and washing. Red blood cells were then stored at −80°C until the analysis.

Glucose and insulin concentrations from the FSIGT will be used to calculate the insulin sensitivity index (S_I_) using Bergman’s minimal model of glucose kinetics [49]. Glucose and c-peptide data will also be used in a two-compartment minimal model of C-peptide secretion and kinetics to calculate insulin secretion rate (ISR) using WinSAAM (version 3.3.0). ISR will then be used in a one-compartment insulin minimal model to determine insulin hepatic extraction index [50].

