#### Comprehensive Metabolite Profiling of the Serum and Muscle Metabolome

For the metabolite analyses, a combined platform of liquid (LC-QTOF-MS) and gas (GCTOF-MS lipids) chromatography coupled to mass spectrometry, in both positive and negative ionization modes will be used. This approach will enable a comprehensive coverage of serum and muscle metabolites with different chemical properties. All sample preparation and analyses will be performed according to a run order design to circumvent methodological biases that may interfere with results interpretation [64]. For example, samples from the same individual are prepared and analyzed in close connection while keeping the internal sample order randomized. Analytical batches will be balanced in terms of treatment group and quality control (QC) samples (ie, pooled from all samples) will be analyzed continuously.

Serum samples will be prepared according to A et al [65], using a 90/10, v/v methanol:water extraction including internal standards for metabolomics; and a 70/30, v/v chloroform:methanol extraction for lipidomics [66].

On an average, we will detect 2000 to 3000 peaks or more, and annotation/identifications will be done via the use of publically available library, in combination with *in house* library at the Swedish Metabolomics Centre (SMC). For targeted analyses and validation of findings, we will use triple quadrupole mass spectrometry techniques, such as LC-QqQ-MSMS or GC-QqQ-MSMS together with LC-TQMSMS and GC-TQMSMS in MRM-mode. Absolute quantification of specific compounds will be achieved by using calibration curves calculated from stable isotope labeled internal standards.

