### Statistics

#### Sample Size Determination

Sample size determination was based on our primary outcome using the study of Nordby et al [80], with a significance level of *P*<.05 and power of 80%. On the basis of the change in normalized glucose clearance (measured using a euglycemic hyperinsulinemic clamp) from pre- to postintervention (12-week aerobic training) compared with the nontrained control group (8.2 [SD 5.9] vs −1.8 [SD 6.2] mL/kg/min FFM/nmoL/L insulin, respectively), 6 participants per group would be required to detect a significant difference between groups. These numbers correspond to those of Ortega et al [81] who compared glucose tolerance tests to detect the insulin sensitizing effects of a bout of continuous exercise and reported that 6 participants would be required to detect a change in insulin sensitivity when using a FSIGT. In order to account for the secondary outcomes, using changes in skeletal muscle glucose transporter (GLUT)4 in response to a 12-week training program as the proxy (0.65 [SD 0.69] vs 0.01 [SD 0.69] AU for training vs control group), 18 women would be required to detect a difference between groups [81]. On the basis of these calculations, and a dropout rate of 10% (2/20), 20 participants per group were selected.

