#### Proposed Statistics

Results will be presented as means (SD), or medians and interquartile ranges for non-normally distributed data. Data will be normalized by log transformation if required. Repeated measures ANOVA will be used to compare differences in the change of outcome variables between the control and exercise groups in response to the exercise/control intervention. Pearson and/or Spearman correlations will be used to examine associations between changes in primary and secondary outcome variables. Data will be analyzed using StataSE (version 14, StatCorp, Texas, USA) and IBM SPSS Statistics 24 (Version 24.0, Armonk, NY, USA).

Comprehensive metabolite profiling data will be evaluated via a combination of multivariate analysis methods and univariate statistics, that is, Principal Component Analysis (PCA), Orthogonal Partial Least Squares (OPLS), and its extensions [64]. In addition, we will perform an extensive validation to determine the model significances, using both internal, ANOVA on the cross-validated model patterns, and external validation, independent sample prediction. Model scores (subject level) will be used to visualize and interpret the differences in metabolic response between predefined patient groups or subgroups, or of individual patients responding differently to the interventions. Model loadings (variable level) combined with univariate *P* values will be used as the base for mechanistic interpretation and to highlight significant metabolites or metabolite patterns.

For bacterial community analysis, basic statistical tests will be performed using QIIME [77] and R software will be used for advanced statistical analysis. Beta-diversity will be evaluated by calculation of weighted and unweighted Unifrac distances. The Shannon and Simpson diversity indices will be employed to study alpha-diversity. The relationship between the composition of the fecal bacteria and exposure variables will be determined using weighted generalized ridge regression methods [82] and the lasso [83]. We will use Dirichlet multinomial models or ecological approaches such as multi-species occupancy models to evaluate interactions and shift in fecal bacterial communities over time [84,85].

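### Metabolomic model scores from one pre/post pair cannot show that individual women respond differently; the clause should be limited to descriptive display

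*Protocol article*

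**What the plan says.** The metabolomics paragraph of Proposed Statistics in the protocol article sets out PCA and OPLS models with univariate tests. It then gives the subject-level output its own role: "Model scores (subject level) will be used to visualize and interpret the differences in metabolic response". The differences in question are those between predefined groups or subgroups, "or of individual patients responding differently to the interventions". The verb covers interpretation as well as plotting.

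On the data behind each score, Overview of Testing Procedures says "Before and following the 12-week intervention, participants completed 4 data collection sessions". The section on fasting blood samples lists, among the uses of the fasting draw at the glucose tolerance test visit, "red blood cell fatty acid composition, metabolomic and lipidomic analysis". Muscle for metabolomics comes from the biopsy in the same testing rounds. No replicate round is described before or after the intervention.

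Two safeguards are stated. In the laboratory, "quality control (QC) samples (ie, pooled from all samples) will be analyzed continuously". In the analysis, "we will perform an extensive validation to determine the model significances", by ANOVA on the cross-validated model and by prediction in independent samples.

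**The concern.** A woman's score change is the sum of her true response to training and whatever would have made her two samples differ anyway: day-to-day biology, sampling and assay error. With one pair per woman the two parts cannot be separated. Women's scores will differ whether or not their responses do, so seeing a difference is not evidence of differing response.

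Neither safeguard closes this gap. Pooled quality control samples address analytical variation and not a woman's own variation between days. Cross-validated ANOVA and external prediction show whether the model as a whole carries signal, and a sound arm-level model is compatible with the same response in every woman.

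At stake is a statement, in a trial whose aim is mechanistic, that particular women respond differently, when the data may show only within-woman variation.

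**Working it through.** **The plan's own figures.** The article gives no figure for the individual-level reading. The inputs borrowed below come from Sample Size Determination: glucose clearance change "8.2 [SD 5.9] vs −1.8 [SD 6.2] mL/kg/min FFM/nmoL/L insulin" (trained vs control) and GLUT4 change "0.65 [SD 0.69] vs 0.01 [SD 0.69] AU for training vs control group". With n per group = 2 × (1.960 + 0.842)² × SD² / difference², they give 2 × 7.85 × 36.6 / 10.0² = 5.7, so 6, and 2 × 7.85 × 0.476 / 0.64² = 18.2, against the stated 6 and 18. The inputs are therefore read as the article meant them.

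**Illustration under an identical response.** Assume that all 20 women who completed the exercise arm have the same true response, that changes are normal, and that the whole SD of change is noise. Call a change at or below zero an apparent non-response. This cut-off is mine; the plan sets none.

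- Per woman: p = Φ(−mean/SD).
- At least one of 20: 1 − (1 − p)^20. Expected number: 20p.
- Clearance: p = Φ(−8.2/5.9) = Φ(−1.39) = 0.082; at least one, 82%; expected 1.6.
- GLUT4: p = Φ(−0.65/0.69) = Φ(−0.94) = 0.173; at least one, 98%; expected 3.5.

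**Do the observed changes discriminate?** Hold the total SD for clearance at 5.9 and let true differences in response make up 0, 25, 50 or 75% of the variance. In simulation the chance of at least one change at or below zero is 82% each time, and the mean gap between highest and lowest woman is about 22 units each time. The exercise-arm changes look the same whatever the truth.

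**Sensitivity to the unknown.** The within-woman SD of the metabolomic scores is not in the article. Let r be the noise SD of change divided by the mean change, with p = Φ(−1/r). The two proxies have r = 0.72 and 1.06.

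| r | P(at least one of 20 at or below zero) |
|---|---|
| 0.1 | about 0% |
| 0.25 | 0.06% |
| 0.5 | 37% |
| 0.72 | 82% |
| 1.0 | 97% |
| 1.5 | 99.7% |

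**What the control arm can add.** Controls carry the same noise without training, so SD_IR = √(SD_exercise² − SD_control²) estimates the spread of true response. With 20 and 15 completers the variance ratio has 19 and 14 degrees of freedom. Power to detect a larger spread in the exercise arm:

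| SD ratio, exercise/control | One-sided 5% test | Two-sided 95% interval |
|---|---|---|
| 1.5 | 46% | 33% |
| 2.0 | 85% | 76% |

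**The case against.** The strongest reply is that the clause commits to little. It sets no threshold, test or responder classification, and an article can leave such detail to the full protocol or analysis plan. The next sentence bases mechanistic interpretation on model loadings with univariate P values and not on individual scores. Controls are profiled too, since analytical batches are balanced by treatment group. Noise is limited by the standardized meal, the overnight fast and running each woman's samples close together. The analysis is secondary, and the Discussion says secondary outcomes may serve as pilot data.

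Most of this stands, and it keeps the point small. It does not remove the point, because the article itself states the interpretation of individuals, and no detail left to another document can separate response from noise in a single pair.

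The objection to the magnitudes also stands. The 82% and 98% come from clearance and GLUT4, not metabolomic scores, and from a cut-off that the plan never sets.

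Three stronger readings are tempting and unsupported:

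- A reader might infer from the near-equal SDs of change (5.9 vs 6.2; 0.69 vs 0.69) that responses do not differ. Those SDs concern other variables in cited studies, come without intervals, and say nothing about metabolomic scores in this trial.
- A reader might infer that responder profiles will become the trial's mechanistic findings. No contrast of responders with non-responders is described.
- A reader might extend the point to responder groups on the insulin sensitivity index. None is planned.

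**Conclusion.** The concern holds as a minor one. The plan states a use of the scores that one pre/post pair per woman cannot support, and the stated validation addresses a different question. That conclusion needs no number; it rests on there being no replicate testing round, and none is described.

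How often a misleading non-responder would appear is not known. It is 82% to 98% if metabolomic scores are as noisy as the two proxies, 37% at a noise-to-mean ratio of 0.5, and negligible at 0.25 or below, all under normality, an identical response and a zero cut-off. The primary analysis and the comparison of arms are untouched.

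**What to change.** Reword the clause in Proposed Statistics so that individual scores are displayed descriptively and no woman is named or profiled as a responder or non-responder from a single pre/post pair. Add that responses will be said to vary between women only if the spread of change in cross-validated scores is larger in the exercise arm than in the control arm, reported as SD_IR with its confidence interval. Otherwise only arm-level differences are reported. State whether the criterion is a one-sided 5% test or a two-sided 95% interval, since the power differs. Even when the criterion is met, it shows that variation exists and not which women carry it, so the bar on individual labels stays.

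The cost is a sentence or two and one variance comparison on data already collected. The downside is imprecision: at 20 vs 15, real heterogeneity with an SD ratio of 1.5 would be missed more often than found, so statements about varying response will often have to be dropped.

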## Results

### Participant Enrollment, Allocation, Follow-Up, and Analyses

Information on participant enrollment, allocation, follow-up, and analysis is shown in Figure 2. Standards of reporting were based on the CONSORT 2010 checklist for randomized control trials. A total of 45 participants were enrolled in the study and randomized into exercise (n=23) and control (n=22) groups. Of these, 10 participants did not complete the intervention (dropout; n=3 exercise, n=7 control) resulting in a final sample of 20 exercise and 15 control participants.

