**Results:**

The final sample included 20 exercise and 15 control participants. Baseline sociodemographics, cardiorespiratory fitness, anthropometry, cardiometabolic risk factors, physical activity, and diet did not differ between the groups (*P*>.05).

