## Methods

### Study Design

In this randomized controlled research study, 45 obese sedentary black SA women were block (2-4 participants) randomized (Microsoft Office, Excel, 2013) into control or experimental (exercise) groups (Figure 1). Block randomization was performed by the project manager after participants completed preintervention testing to ensure that investigators performing the testing were blinded to group allocation. The exercise group completed 12 weeks of supervised combined aerobic and resistance training (40-60 min, 4 days/week) but maintained their usual dietary behaviors. The control group were instructed to continue their habitual physical activity and dietary behaviors and to refrain from initiating any exercise programs. Before and following the 12-week intervention period (exercise or control), insulin sensitivity and secretion (primary outcome), as well as the proposed determinants of insulin sensitivity and secretion (secondary outcomes) were measured. In addition, dietary intake, sleep quality and quantity, physical activity, and sedentary behavior were monitored for a minimum of 4 days every 4 weeks.

This study was approved by the Human Research Ethics Committee at the University of Cape Town (HREC REF:054/2015). The study was performed in accordance with the principles of the Declaration of Helsinki (1964, amended last in Fortaleza Brazil, 2013), ICH Good Clinical Practice (GCP), and the laws of SA. Participants provided written informed consent before participation in the screening and the research study. Participant recruitment and testing procedures occurred over an 18-month period, between July 2015 and December 2016. Sample and data analysis began in January 2017 and are currently ongoing.

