### Participant Baseline Characteristics

The sociodemographic characteristics of the participants at baseline are presented in Table 1. The average age of the whole group (n=45) was 24 (SD 4) years. Sociodemographic characteristics were not different between participants of the exercise, control, and dropout groups. The majority (67%, 30/45) of participants had completed at least grade 12 education, and 27% (12/45) of participants were currently enrolled students, while 51% (23/45) were employed. A quarter of the participants earned less than R2500/month (US $210/month at exchange rate of R11.9/US $, 13 February 2018), whereas 42% (19/45) earned between R2500-R5000/month (US $210-420/month), and the remaining participants (31%, 14/45) earned greater than R5000/month (US $420/month). Most of the participants were not married (89%, 40/45) and 42% (23/45) had at least 1 child. Apart from hypertension (42%, 19/45) and diabetes (13.6%, 6/45), the known family history of disease was relatively low.

**Table 1 table1:** Baseline sociodemographic characteristics.

Variables		Control (n=15)	Exercise (n=20)	Dropout (n=10)	*P* value
Age in years, mean (SD)		24 (4)	23 (3)	26 (4)	.24
Informal housing, n (%)		6 (40)	4 (20)	6 (60)	.09
Housing density (persons/room), median (interquartile range)		1.3 (1.0-1.6)	1.0 (0.8-1.5)	1.0 (1.0-2.7)	.38
Asset index (% of 14 commodities), n (%)		53 (15)	54 (20)	47 (23)	.62
**Education, n (%)**					.87
	< Grade 12	6 (43)	5 (25)	3 (30)	
	Grade 12	5 (36)	9 (45)	4 (40)	
	Tertiary	3 (21)	6 (30)	3 (30)	
**Employment, n (%)**					.63
	Employed	9 (60)	10 (50)	4 (40)	
	Student	5 (33)	9 (45)	4 (40)	
	Unemployed	1 (7)	1 (5)	2 (20)	
**Income, n (%)**					.09
	R0-2499/month	6 (40)	2 (10)	4 (40)	
	R2500-R4999/month	7 (47)	8 (40)	4 (40)	
	>R5000/month	2 (13)	10 (50)	2 (20)	
Marital status, married, n (%)		1 (7)	3 (15)	1 (10)	.73
**Parity, n (%)**					.33
	None	7 (48)	15 (75)	4 (40)	
	1 child	4 (27)	2 (10)	3 (30)	
	2-3 children	4 (27)	3 (15)	3 (30)	

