Although 118 women were screened, only 45 women were willing and eligible to be enrolled in the study. A requirement for screening was to consent for HIV testing, which deterred many potential participants from screening and is likely related to the high rates (20%) of HIV in women in the City of Cape Town [87]. The main reasons for ineligibility after screening included (1) not meeting the BMI criteria, (2) not using injectable contraception, and (3) time limitations and/or the invasiveness of procedures involved in the study. The injectable contraception was chosen as part of the selection criteria to ensure a more homogenous participant profile. The injectable contraception is freely available to all women in the community clinics and is thus the contraception of choice for the majority of women. Of the 45 women recruited, 35 completed the 12-week intervention, with the greatest dropout being in the control group (7 out of the 10 participants; Figure 1). This may be explained by the control groups’ disappointment on not being assigned to the exercise group, resulting in a lack of commitment and loss of interest in the study. This occurred despite the assurance that the control group could participate in the 12-week exercise intervention following the 12-week control period, for which they would be reimbursed for their time, inconvenience, and travel. Interestingly, only 9 of the 15 control participants initiated the exercise training, of which 6 attended more than 30 of the 48 training sessions, and 3 participants attended less than 3 sessions. In contrast, there was a low dropout rate in the exercise group (3 out of the 10 participants). It is anticipated that the outcomes from the focus group and informant interviews will provide insight regarding the reasons for the discrepancies in the dropout rates between the groups.

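### The planned contrast uses 20 and 15 completers of 23 and 22 randomised and compares raw change, so it relies on dropout within each arm being unrelated to change; the baseline tables cannot show whether that is plausible.

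*Protocol article*

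**What the plan says.** The Results give 45 randomised (23 exercise, 22 control) and ten who did not complete (3 exercise, 7 control), "resulting in a final sample of 20 exercise and 15 control participants". The Abstract repeats this final sample. Proposed Statistics compares the change in each outcome between arms by repeated measures ANOVA and names no wider analysis set. Sample Size Determination allowed for 10% dropout.

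Tables 1-3 have three columns (control 15, exercise 20, dropout 10) and one P value per row across the three. From these the Results conclude: "Sociodemographic characteristics were not different between participants of the exercise, control, and dropout groups". The Abstract goes further: "Baseline sociodemographics, cardiorespiratory fitness, anthropometry, cardiometabolic risk factors, physical activity, and diet did not differ between the groups", at P>.05.

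The Discussion acknowledges the uneven loss and says it may reflect control women's disappointment at their allocation. It does not discuss what this means for the comparison. It describes the exercise arm thus: "there was a low dropout rate in the exercise group (3 out of the 10 participants".

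Study Design says: "Block randomization was performed by the project manager after participants completed preintervention testing".

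**The concern.** Randomisation makes the 23 and 22 comparable. It does not make the 20 and 15 comparable if the women who left would have changed differently from those who stayed. Loss is about two and a half times as high in the control arm, and the one explanation offered can act only in that arm. Both primary outcomes (insulin sensitivity and secretion) and every association between changes rest on the same completers.

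The evidence offered for comparability is the set of three-group P values. Because dropouts are removed from their arms, a reader can check neither 23 vs 22 nor whether dropouts resembled the women who stayed in the same arm. A non-significant three-group test with 15, 20 and 10 women is weak evidence in any case.

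**Working it through.** **The plan's own sample size.** Inputs from Sample Size Determination: difference 8.2 − (−1.8) = 10.0; SDs 5.9 and 6.2, pooled √((5.9² + 6.2²)/2) = 6.05; alpha .05 (two-sided assumed) and 80% power. Then n per group = 2 × (6.05 × (1.960 + 0.842)/10.0)² = 5.75, so 6, matching "6 participants per group would be required to detect a significant difference between groups". The planned size of 20 follows from the 18 stated for the GLUT4 outcome: 18/0.90 = 20. The planned primary effect is 10.0/6.05 = 1.65 SD. Power for it at 20 vs 15 exceeds 99%, so the issue is possible bias, not power.

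**Dropout.** Exercise 3/23 = 13.0%; control 7/22 = 31.8%; overall 10/45 = 22.2%. Fisher's exact test for unequal loss gives P = .17. With 45 women that neither establishes a difference nor shows balance.

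**How far the completer contrast could be off.** Let δE and δC be the amounts by which dropouts' mean change differs from that of completers in each arm. An arm's mean over all randomised women is the completer mean plus (dropout fraction × δ). The completer contrast (exercise minus control) is therefore off by

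error = (7/22)·δC − (3/23)·δE.

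The documents give no value for either δ, so these are assumptions. Planning units use SD 6.05.

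| Assumption | Error | δ = 0.5 SD | δ = 1 SD | δ = 1 SD, planning units (effect 10) |
|---|---|---|---|---|
| Same δ in both arms | 0.19δ | 0.09 SD | 0.19 SD | 1.1 |
| Control dropouts only | 0.32δ | 0.16 SD | 0.32 SD | 1.9 |
| Opposite signs | 0.45δ | 0.22 SD | 0.45 SD | 2.7 |

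**Change score or baseline adjustment.** With two time points, the group-by-time test in a repeated measures ANOVA is the two-sample test on change. Suppose baseline and post-test have equal SDs and correlation ρ. The slope of change on baseline is then −(1 − ρ). If dropout leaves control completers with a baseline mean b SD away from that of all randomised controls, the change contrast moves by (1 − ρ)·b in size. For ρ = 0.5 and b = 0.2 (assumed) that is 0.10 baseline SD. A linear adjustment of the post-test for baseline removes this component.

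**Does a mixed model recover the 45?** With one baseline, one post-test and a covariance common to both arms, the likelihood splits into a baseline part and a post-given-baseline part. The arm effect sits only in the second, to which women without a post-test do not contribute. Fitting both models to a simulated 23 vs 22 dataset with 3 and 7 post-tests missing gave 1.0323 from the common-baseline maximum likelihood model and 1.0323 from completer ANCOVA.

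**Baseline tables, two groups against three.**

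| Variable | Control vs exercise completers | Two-group P | Three-group P, recomputed | Printed |
|---|---|---|---|---|
| Height | 1.62 (.06) vs 1.57 (.06) m | .020 (.003 to .08 allowing for rounding) | .058 | .05 |
| Income, three bands | 6, 7, 2 vs 2, 8, 10 | .033 (chi-square) | .089 | .09 |
| Income above R5000 | 2/15 vs 10/20 | .034 (Fisher) | – | – |

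**Pretesting.** Table 3 has blood pressure and HbA1c for 4 of 10 dropouts and 35 of 35 completers. Table 2 has VO2peak for 9 of 10 dropouts and ActivPAL data for 7 of 10. Study Design places randomisation after completed pretesting.

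**The case against.** The case on the other side has several parts.

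- **Nothing has been reported.** Analysis was ongoing at publication, and an article may leave missing-data rules to a fuller plan. It stands that no outcome contrast can be called biased. But the completer sample is stated twice and the change analysis is named, so this is a choice made in the article and not a gap.
- **The size is modest.** The errors above are 5% to 27% of the planned primary effect, and the δ values are assumed. This stands and limits the seriousness. Effects smaller than the planned one would be proportionately more exposed.
- **Arm-driven dropout.** A reader might infer that control loss was caused by the allocation and that the result is therefore biased. The article says only that disappointment may explain it and leaves the reasons to focus groups and interviews. Dropout that differs by arm also does not bias the contrast unless, within an arm, it is related to change.
- **Imbalances.** A reader might take height and income as damage done by dropout. The tables cannot show that. They print 34 P values, so about 34 × .05 = 1.7 below .05 are expected by chance, and weight (P=.52) and BMI (P=.72) suggest nothing. The two rows show only that the three-group tests are weak reassurance.
- **Modelling all 45.** A reader might expect a mixed model on everyone randomised to restore the randomised comparison. As shown in the working, it equals completer ANCOVA.
- **The 3 out of 10.** This is the exercise share of all dropouts, and the Results give correct arm counts. The count is right, but calling it a dropout rate is not.
- **Table 3.** Blood pressure and HbA1c were also needed at screening, so 4 of 10 may be a tabulation gap and not missed pretesting.

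**Conclusion.** The concern holds in limited form and should be fixed. The article commits to 20 vs 15 completers of 23 vs 22 randomised, after loss of 13.0% against 31.8%, and to a change-score analysis that does not allow dropout to depend even on baseline. Under the assumed differences of 0.5 to 1 SD, the error runs from 0.09 to 0.45 SD depending on the pattern. Its actual size and direction are unknown, and the documents do not show that bias occurred.

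Tables 1-3 are laid out so that they describe neither the randomised arms nor the comparison to be analysed. The Abstract's claim of no baseline difference at P>.05 is not firmly supported: height is printed at .05, and income differs noticeably between completer groups, possibly by chance.

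**What to change.** 1. Replace the change-score repeated measures ANOVA with a baseline-adjusted analysis of the post-test (ANCOVA, or the equivalent common-baseline mixed model). State that women without a post-test add no information on the arm effect, and label the result as 20 vs 15 under missing at random.
2. Add a missing-not-at-random sensitivity analysis covering all 45 as randomised, for both primary outcomes: a tipping-point analysis with separate deltas for each arm. This is the only step that addresses dropout related to unobserved change.
3. Tabulate baseline by randomised arm (23 vs 22), with completers and dropouts shown within each arm, and remove the claim that the groups did not differ.
4. In the Discussion, give dropout rates as 3/23 and 7/22.
5. Reconcile the Study Design statement on pretesting with the missing dropout data in Tables 2 and 3, and say how many dropouts have a baseline FSIGT. Resting blood pressure and the FSIGT share the overnight visit, so this affects how the second step is carried out.

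The cost is modest: revised analysis wording, one sensitivity analysis, a re-cut table and two corrections, with no new data. The downside is an explicit missing-at-random assumption in the main analysis, which the second step is there to probe.
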